##### Economic evaluation

The Client Service Receipt Inventory (CSRI) [46] measures the use of healthcare/social care services and other economic impacts. This questionnaire measures direct costs (emergency services/hospital admissions use, specialised medical consultations, prescribed diagnostic trials and consumed medication) and indirect costs (absenteeism and quantity/quality of job performance on a 100-point scale). Delivery will be by the use of an adapted Spanish version [47] in a self-reporting format.

#### Subsidiary measures

##### Maladjustment to daily life scale

The Maladjustment Scale (IG) [48] is used to assess the degree to which emotional dysregulation affects daily life functioning in psychiatric patients. It is a 6-item self-report questionnaire rated using the 6-point Likert scale, ranging from 0 (not at all) to 5 (very strong). This test has a cut-off point of 12 for the full scale and 2 points for each item. The higher score, the greater maladjustment. It has a high internal consistency (α = .94) and high diagnostic efficiency (90%), showing sensitivity to therapeutic changes.

##### Credibility/expectancy questionnaire

Satisfaction with treatment is assessed by the CEQ [43]. It is a brief 6-item questionnaire covering how logical the treatment seemed, the extent of patient satisfaction, whether other psychological problems could benefit from it, its usefulness for the patient’s specific problem and to what extent the treatment was aversive, rated on a scale from 0 (not at all) to 10 (very strong). This instrument has demonstrated high internal consistency (α = .79 for expectancy and α = .81 for credibility) and good test-retest reliability (*r* = .82 for expectancy and *r* = .75 for credibility) [49]. The questionnaire is delivered post-treatment and at 15 months after the baseline.

##### Perceived subjective global improvement

Participants will be asked at the end of the study on a 7-point ad hoc Likert scale from much/quite/little bit better, the same or much/quite/little bit worse compared to when they entered the study. Since BPD patients usually have a distorted perception about themselves, the same scale will be used to closely evaluate the perceived impressions of a family member or friend.

#### Baseline variables

##### Socio-demographic variables

Gender, age, marital status, parent’s nationality, cohabitation, educational level and occupational status will be included in the study.

#### Study integrity

This study has been approved by the Provincial Ethics Committee of Málaga (Spain). The study has been developed in accordance with CONSORT guidelines.

#### Sample size

The sample size calculation is based on our primary outcome measure, BPD symptom severity at 12 months. A sample size of 26 participants per group is required to detect a post-treatment effect size of 0.20 (Cohen’s d) between both groups with a power of 0.80 in a one-tailed test and with a 95% confidence level. This corresponds to the estimated differences between groups of about 8.6 BSL-23 raw scores. Therefore, the total sample size is determined at 52 participants. Dropout rates for BPD patients are 24% to 52% [50]; therefore, we need to recruit at least 72 individuals.

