#### Primary outcome measure

##### Severity of borderline personality disorder

We will use the Spanish version of the BSL-23 [44]; it replicates the one factor structure of the original and shows high reliability (*α* = .95) as well as good test-retest stability when checked in a subsample of 74 patients (*r* = .73 *p* < .01). The BSL-23 [45] is one of the most widely used questionnaires (in its short form) in psychotherapy trials. It has 23 self-answer questions rated on a scale of 1 to 5 on the Likert scale, ranging from 0 (not at all) to 4 (very strong). The BSL-23 is very reliable in the diagnosis of BPD, and as evidenced by Cronbach’s alpha of .93, its one factor structure makes it highly constant.

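### The stated effect size (Cohen's d 0.20) fits neither 26 per group nor the 8.6-point difference: at d = 0.20, 26 per group give about 18% power, not 80%

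*Protocol article*

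**What the plan says.** The whole justification of the trial's size is one paragraph, in the Sample size section of the protocol article's Methods. It states that "A sample size of 26 participants per group is required to detect a post-treatment effect size of 0.20", and names the metric: "effect size of 0.20 (Cohen’s d) between both groups". The operating conditions follow: "with a power of 0.80 in a one-tailed test", and a 95% confidence level, that is, alpha 0.05. The paragraph then turns the effect into points on the primary outcome scale: "This corresponds to the estimated differences between groups of about 8.6 BSL-23 raw scores". The total is 52, and recruitment is raised to 72 to allow for dropout.

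The paragraph gives no standard deviation, no correlation between measurements and no repeated-measures assumption. The primary outcome section describes the BSL-23: "It has 23 self-answer questions rated on a scale of 1 to 5 on the Likert scale, ranging from 0 (not at all) to 4".

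**The concern.** A standardised difference of 0.20 is conventionally small, and trials that detect it with 80% power need several hundred patients per arm. Twenty-six per arm is typical of a medium-to-large effect. The paragraph gives enough to test the claim: the group size, the metric, the power, the sidedness, the confidence level and a raw-score equivalent.

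The paragraph tells readers that the trial can detect a small benefit on its primary outcome. If that is wrong, a non-significant result could be read as ruling out small benefits when the trial had little chance of showing one. The target in points cannot be checked either, because no SD links it to the standardised effect.

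**Working it through.** **Inputs.** From the Sample size section: n = 26 per group, d = 0.20, power 0.80, one-tailed, alpha 0.05, raw difference 8.6. From the primary outcome section: 23 items scored 0 to 4, so a sum score of 0 to 92; the test-retest correlation of 0.73 is used only in step 5. Allocation is 1:1.

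**1. The plan's own figure.** For two means with equal groups, n per group = 2 × [(z₁₋α + z_power)/d]².
- One-tailed: 2 × [(1.645 + 0.842)/0.20]² = 309.1, so 310 per group. The noncentral t also gives 310.
- Two-tailed: 393 by the same formula, 394 by the noncentral t.

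The stated 26 is not reproduced. The required number is about 12 times larger (310/26 = 11.9).

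**2. Power of 26 per group at d = 0.20.** The noncentrality is d × √(n/2) = 0.20 × √13 = 0.721, on 50 degrees of freedom.
- One-tailed: 0.175 (normal approximation 0.178).
- Two-tailed: 0.109.

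**3. What 26 per group can detect.** The detectable d is (1.645 + 0.842) × √(2/26) = 0.69 by the normal approximation and 0.70 by the noncentral t, one-tailed at 80% power. The two-tailed values are 0.78 and 0.79.

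**4. The 8.6 points.**
- If d = 0.20, the SD is 8.6/0.20 = 43. The largest SD possible on a scale 92 points wide is 92/2 = 46, reached only with half the patients at each extreme. Coding the items 1 to 5 leaves the width, and so this ceiling, unchanged.
- If d = 0.70, the SD is 8.6/0.70 = 12.3.

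The document gives no SD, so the power for 8.6 points with 26 per group (one-tailed t test) is shown over assumed values:

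| Assumed SD | d for 8.6 points | Power |
|---|---|---|
| 12.3 | 0.70 | 0.80 |
| 15 | 0.57 | 0.65 |
| 20 | 0.43 | 0.45 |
| 43 | 0.20 | 0.18 |

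**5. Could an unstated refinement rescue d = 0.20?** Here the test-retest correlation of 0.73 is assumed to apply between baseline and follow-up.
- Baseline-adjusted analysis: 309.1 × (1 − 0.73²) = 144.4, so 145 per group; power with 26 is about 27–28%.
- Change score: 309.1 × 2 × (1 − 0.73) = 166.9, so 167 per group; power with 26 is about 25%.
- For 26 per group to suffice after adjustment, the correlation would have to be √(1 − 26/309.1) = 0.96.
- If all 72 recruited patients were evaluable (36 per group, no adjustment), one-tailed power would be 21%.

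**6. Could 0.20 be another metric?** Read as Cohen's f for a group-by-time interaction with two measurements and an assumed correlation of 0.5, the noncentrality is N × 2 × 0.20²/(1 − 0.5). At N = 52 this is 8.32 and power is 0.807; at N = 50 power is 0.791. This variant returns exactly 52. With f = 0.10, the equivalent of d = 0.20, the same test needs N = 200.

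**The case against.** The strongest reply is that the label, not the sample size, is wrong. The Cohen's f reading in step 6 returns exactly 52 patients, so the authors may have run a coherent repeated-measures calculation and misnamed its effect size. This is plausible but remains conjecture: it assumes a correlation of 0.5 and two time points, whereas the Data analyses section models three. It also does not save the paragraph, which names Cohen's d and a one-tailed test. Under that reading the detectable difference in change is 4 × 0.20 = 0.8 SD, again far from small. It does affect the order of the remedy: the metric has to be identified before the number is corrected.

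A second reply is that the 18% belongs to an unadjusted two-group t test, while the planned analysis is a GEE that uses baseline data. That is right as to scope, and the 18% should be quoted with its test. Adjustment at the assumed correlation lifts it only to about 27%.

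A third reply concerns the 8.6 points. An SD of 43 is below the ceiling of 46, so it is implausible rather than impossible, and the SD of 12.3 is solved backwards from 26 per group. The powers in step 4 also ignore baseline; with adjustment at 0.73 they become about 0.98, 0.91 and 0.72 at SDs of 12.3, 15 and 20. This stands: whether 8.6 points is an adequately powered target depends on an SD and a test that the paragraph does not give. An SD may be stated in a fuller protocol, so its absence is not in itself the error. The mismatch between d = 0.20 and 26 per group does not depend on any SD.

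**Conclusion.** The concern holds. For the metric, test, confidence level and group size that the paragraph names, power at d = 0.20 is 0.175 rather than 0.80. The number required is 310 per group rather than 26, and the effect detectable with 26 is d of about 0.70. These results rest on a two-group comparison of means with 26 evaluable patients per arm and no covariate. No variant that keeps Cohen's d at 0.20 comes close to 26 per group unless the baseline correlation is about 0.96.

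The raw-score translation supports the same conclusion less firmly, because it depends on an SD that is not stated: d = 0.20 would require an SD near the scale's ceiling. Nothing elsewhere in the document corrects the paragraph. Since it is the only statement of what the trial can detect on its primary outcome, it must be fixed.

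**What to change.** Rewrite the Sample size paragraph in this order.

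1. State what was actually calculated: the effect-size metric, the test, its sidedness, the number of measurements and any correlation assumed.
2. State the BSL-23 SD and its source, and show how 8.6 points follows from it.
3. Remove d = 0.20 or relabel it. If the calculation was a two-group comparison, say that 26 per group give 80% power (one-tailed 0.05) for d of about 0.70, which equals 8.6 points only if the SD is about 12.3. If 0.20 was Cohen's f, say so, and give the corresponding difference in SD units and in points.
4. Show power over a plausible range of SDs, and say what the recruited sample can detect. With no dropout, 36 per group would detect d of about 0.59 (one-tailed t test, 80% power). With 26 evaluable per group the figure is 0.70.

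The cost is the wording of one paragraph. No extra enrolment is proposed and the design does not change. The price is a much less favourable, but accurate, statement of the effect that the trial can detect.

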### Study aims

The aim of the study is to investigate, by comparison with Structured Support Therapy, how effective Iconic Therapy is in improving participants’ BPD symptoms. The primary outcome measure is a change of symptoms measured through the use of the Borderline Symptom List (BSL-23) post-treatment. Our hypothesis is that patients undergoing Iconic Therapy will show a greater reduction in the severity of their symptoms after receiving the intensive part of the therapy than those undergoing Structured Support Therapy. As a secondary outcome, we hypothesise that these differences will continue to be verifiable at the 12-month follow-up. Other secondary measures are suicidal ideation, suicidal behaviour, maladjustment to daily life and use of services as a consequence of BPD symptoms. We will also evaluate satisfaction with the treatment and perceived subjective global improvement beyond the symptoms.

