#### Data analyses

Patients will be included in intent-to-treat analyses. Participants’ demographic characteristics will be summarised using descriptive statistics, and the comparability of the treatment groups will be examined using *χ*^2^ tests for categorical variables and *t* tests for continuous variables.

Data analyses of the primary and secondary outcomes will be conducted using generalised estimating equation (GEE) models. Essentially, GEE models extend generalised linear models (GLMs) to allow analysis of repeated measurements or other correlated observations. The response can be scale, counts, binary or events-in-trials. In addition, GEE models can also deal with data that have missing values as long as the missing value is completely random. Parameter estimation can still yield robust results [51].

In these GEE models, treatment conditions (experimental vs. control) will be included as the between-subjects factor and time (baseline, after treatment and at 12 month follow-up) as the repeated measure. Main effects and interaction between treatment and time will be examined. When the interaction effect is statistically significant, simple main effects analyses will be conducted.

IBM SPSS (version 22.0 for Windows) will be used for the statistical data analyses. Statistical significance will be defined as *p* < .05. Bonferroni correction will be applied for post hoc multiple comparisons.

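### The stated 80% power is for a one-tailed test, but the planned GEE analysis turns on a non-directional 2-df interaction test, so the power figure does not belong to the analysis

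*Protocol article*

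**What the plan says.** The Sample size section of the protocol article states: "A sample size of 26 participants per group is required". The target there is a standardised difference (Cohen's d) of 0.20, and the test conditions are specified as "with a power of 0.80 in a one-tailed test and with a 95% confidence level". It adds: "This corresponds to the estimated differences between groups of about 8.6 BSL-23 raw scores". It gives no SD and no correlation between visits.

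The Data analyses section describes GEE models with treatment as the between-subjects factor and time (baseline, after treatment, 12-month follow-up) as the repeated measure. "Main effects and interaction between treatment and time will be examined". Simple main effects are analysed only when the interaction is significant, and post hoc comparisons are Bonferroni-corrected. The threshold is given as "Statistical significance will be defined as *p* < .05". The section does not say whether tests are one-tailed or two-sided.

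The Study aims section states a directional hypothesis: "patients undergoing Iconic Therapy will show a greater reduction in the severity of their symptoms" after the intensive part of the programme than those in the comparator.

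**The concern.** A power statement is a property of a particular test. Here the calculation uses a one-tailed 5% test, while the analysis opens with a test that has no direction and makes the follow-up comparisons depend on it. A reader or ethics committee is told that the chance of missing the targeted effect is 20%, but that figure does not carry over to the analysis described.

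The mismatch is distinct from the separate problem that d = 0.20 and 26 per group are incompatible. Correcting the effect size alone would still leave a power claim for a one-tailed test that the analysis section does not contain. The comparator is also an active group programme covering emotion regulation, social skills, mindfulness and relapse prevention (Table 2). A difference in its favour is possible and would matter. That is a reason to prefer a two-sided test; it is not itself a contradiction in the text.

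**Working it through.** **Inputs from the documents.** 26 per group, d = 0.20, 8.6 BSL-23 points, power 0.80, one-tailed, 95% confidence (taken as alpha = 0.05) from Sample size; two arms, three visits and p < .05 from Data analyses.

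**Step 1: degrees of freedom of the gatekeeping test.** (2 − 1) × (3 − 1) = 2. A joint test on 2 df has no single direction, so it cannot be one-tailed.

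**Step 2: try to reproduce the plan's figure.** For a two-sample comparison, n per group = 2(z_α + z_0.80)² / d².
- One-tailed: 2(1.645 + 0.842)² / 0.04 = 309.1, so 310 per group.
- Two-sided: 2(1.960 + 0.842)² / 0.04 = 392.4, so 393 per group.

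The stated 26 is not reproduced. Power at 26 per group and d = 0.20 (noncentral t, 50 df, noncentrality 0.20 × √13 = 0.72) is 0.175 one-tailed and 0.109 two-sided. The normal approximation gives 0.178 and 0.108.

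**Step 3: conditional illustration.** Accept n = 26, one-tailed 5% and 80% power as true, and solve for d.
- Normal approximation: (1.645 + 0.842) × √(2/26) = 0.69. Noncentral t: 0.699.
- Two-sided 5% power at that d with 26 per group: 0.701 (normal), 0.696 (t).
- The d that gives 80% two-sided power with 26 per group (t): 0.792.
- Group size for 80% two-sided power at d = 0.699 (t): 34 (power 0.811; 33 gives 0.799).

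**Step 4: the raw difference.** 8.6 / 0.20 implies an SD of 43; 8.6 / 0.699 implies an SD of 12.3. With no SD in the document, neither can be confirmed. If the SD were 12.3, d = 0.792 would be about 9.7 points.

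**Step 5: how far the illustration depends on the visits.** Step 3 is a comparison at a single visit. For change from baseline, with equal variances and correlation r between visits, the standardised effect becomes d / √(2(1 − r)). With d = 0.699 and 26 per group, two-sided power is:

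| Assumed r | Two-sided power |
|---|---|
| 0.3 | 0.55 |
| 0.5 | 0.70 |
| 0.73 | 0.92 |

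The value 0.73 is the BSL-23 test-retest correlation in the Primary outcome measure section, used here only as a probable upper bound. The 70% therefore carries over to a change-from-baseline contrast only near r = 0.5.

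**The case against.** The strongest reply has four parts.

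1. **Sidedness is not stated in the analysis section.** The hypothesis is directional, and a post-treatment comparison of the two arms is a 1-df contrast that could be tested one-tailed; that detail might sit in an analysis plan not shown here. This stands to the extent that a two-sided test of the 1-df contrast is an inference. It does not rescue the power statement: the protocol itself makes simple effects conditional on a 2-df interaction, and a directional hypothesis does not make that test one-tailed.

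2. **The effect behind the 70% is not the sponsor's.** A reader might infer that the trial has about 70% power for the effect it was sized on. The documents do not support that. The only standardised effect stated is d = 0.20, where two-sided power is about 11%; d = 0.70 appears nowhere and is obtained only by setting 0.20 aside.

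3. **Another origin for 52 is possible.** A group-by-time F test with f = 0.20 (not d), two time points and an assumed correlation of 0.5 gives 52 in total (power 0.807). That test is already non-directional, so no fall to 70% would follow. This origin is also an assumption and conflicts with both Cohen's d and the one-tailed test in the text. If it were true, the one-tailed statement would still need correcting.

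4. **The 70% is not GEE power.** It comes from a two-sample t test at one visit, while the power of the planned model depends on the correlation between visits. This stands in full, and is why the figure is only an illustration.

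**Conclusion.** The point holds as an inconsistency: the 80% is stated for a one-tailed 5% test, the planned analysis names no such test, and its gatekeeping interaction is non-directional. This rests on the text alone and needs no assumed effect size.

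The size is conditional. Taking 26 per group, one-tailed 5% and 80% at face value in a simple two-sample comparison, moving to a two-sided test lowers power from 80% to about 70%, or raises the effect detectable with 80% power from d of about 0.70 to about 0.79. At the effect actually stated, d = 0.20, power is about 18% one-tailed and 11% two-sided. Neither set of figures is the power of the GEE interaction test, which cannot be computed without an SD, a between-visit correlation and an assumed pattern of effect over the visits. The document does not show which of its inputs is the wrong one.

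**What to change.** In Data analyses, name the primary contrast (the between-group difference in BSL-23 change from baseline to post-treatment, in line with Study aims) and state that it is tested two-sided at 0.05.

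In Sample size, replace the one-tailed statement with the power, or the smallest detectable effect, for that two-sided contrast at 26 evaluable per group. Give the assumed SD and between-visit correlation, and reconcile the result with d = 0.20 and 8.6 points. The same sentences should settle the time point, since that section calls the primary outcome severity at 12 months and then sizes on a post-treatment effect. Do not print d = 0.70 as the trial's target; it is a back-calculation and not a stated design value.

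The cost is a few sentences and a less favourable stated power or detectable effect. No extra patients and no change of design are required.

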**Methods/Design:**

Our study will be a controlled 12-month pragmatic, two-armed RCT. A total of 72 young people (15 to 25 years old) with suicidal ideation/self-injuring behaviour and BPD traits and symptoms will participate in the study. The subjects will be randomised into two groups: Iconic Therapy or Structured Support Therapy. The participants will be assigned to either group on a 1:1 basis. Both the Iconic Therapy and the Structured Support Therapy programmes consist of 11 weekly sessions delivered by two trained psychologists in a group format of between 8 to 12 outpatients. The primary outcome will be measured by the change in symptom severity. Secondary outcomes include changes in suicidal ideation/ behaviour, non-suicidal self-injury, maladjustment to daily life and cost-effective analysis. The primary outcome will be a decrease in the severity of BPD symptoms as assessed by the Borderline Symptom List (BSL-23). For the clinical evaluation, three study assessments will take place: at baseline, after treatment and at 12-month follow-up. We hypothesise that patients attending the Iconic Therapy group will show a significantly higher reduction in symptoms than those in the Structured Support Therapy group. Data will be analysed using generalised estimating equation (GEE) models.

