Specific therapies of this type may help sustain BPD sub-threshold symptoms and decrease health service and non-health care related costs derived from BPD diagnosis. Validating a treatment that has been showing good clinical results on severe BPD symptoms is not only an encouraging point of departure but also a priority. In this study, we test Iconic Therapy against Structured Support Therapy. We did not compare Iconic Therapy with any specialised treatment for BPD (i.e., DBT, TFT or MBT), as our objective was to empirically support that Iconic Therapy is more effective in reducing BPD symptoms than non-specialised treatment.

Finally, a number of potential limitations should be indicated. First, the sample size is small, and this may alienate results from its generalisation. Second, the age range for recruitment is limited (15 to 25 years old); therefore, the recruitment flow may be delayed. Third, heterogeneity on suicidal ideation severity and self-injuring behaviour frequency/lethality may affect treatment adherence, although symptom severity does not seemingly affect adherence to prescriptive therapies [59]. Fourth, the expected rate of dropouts for BPD is high (24% to 58%), and a high dropout rate may slant results [50]. Fifth, the 30 min shorter duration of the Structured Support Therapy group might interfere with the placebo control effect. Sixth, we used self-report questionnaires and not structured clinical interviews, which could represent a limitation despite the adequate psychometric properties of the instruments used.

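### The recruitment target of 72 preserves 52 evaluable participants only if loss is at most 27.8%, so it does not follow from the quoted dropout range of 24% to 52% (58% in the Discussion)

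*Protocol article*

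**What the plan says.** The Sample size section of the protocol article sets the evaluable number: "A sample size of 26 participants per group is required to detect a post-treatment effect size of 0.20 (Cohen’s d) between both groups". The calculation is for 80% power, one-sided, at the 5% level. The section gives the raw-score equivalent as 8.6 BSL-23 points and concludes: "Therefore, the total sample size is determined at 52 participants".

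It then moves from evaluable to recruited participants in one sentence: "Dropout rates for BPD patients are 24% to 52% [50]; therefore, we need to recruit at least 72 individuals". No single dropout rate is named as the one used.

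The limitations paragraph of the Discussion cites the same reference with a different upper limit: "the expected rate of dropouts for BPD is high (24% to 58%), and a high dropout rate may slant results [50".

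The Abstract and the Study design section both fix the trial at 72 participants, allocated 1:1.

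**The concern.** The recruitment figure is presented as a consequence of the whole dropout range, but a single number can preserve 52 evaluable participants only up to one particular rate. If that rate lies near the lower limit, the plan has made an allowance for mild attrition only, and the text does not say so. A reader would take the planned power as protected against the dropout the authors quote.

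The two upper limits, 52% and 58%, carry the same citation. They cannot both be the figure meant, and the size of any shortfall at the top of the range depends on which one is.

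**Working it through.** **Inputs.** Evaluable total 52 (26 per group), one-tailed test at the 5% level, power 0.80, recruited total 72, and dropout 24% to 52%: all from Sample size. Upper limit 58%: from the Discussion. Allocation 1:1: from the Abstract. The 38% used below is the midpoint of 24% and 52%; the protocol does not state it.

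**Step 1: trying to reproduce 72.** The usual inflation is N = 52/(1 − d), where d is the proportion lost.

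- d = 0.24: 52/0.76 = 68.4, so 69
- d = 0.38: 52/0.62 = 83.9, so 84
- d = 0.52: 52/0.48 = 108.3, so 109
- d = 0.58: 52/0.42 = 123.8, so 124

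None of these is 72. The alternative 52 × (1 + 0.38) = 71.8 does round up to 72. That would be the wrong inflation formula applied at the midpoint, but the protocol does not describe its method, so this origin is only a conjecture.

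**Step 2: the loss that 72 can absorb.** 1 − 52/72 = 20/72 = 27.8%. The target therefore covers 24% to 27.8% and nothing above. By length, the uncovered part is (52 − 27.8)/(52 − 24) = 24.2/28, about 87% of the interval, or (58 − 27.8)/(58 − 24) = 30.2/34, about 89% with the Discussion's limit.

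**Step 3: what the shortfall does to power, on a stated condition.** Take as given that 26 per group yields 80% one-tailed power. A two-sample t calculation then implies a standardised difference of about 0.70. This value is back-calculated and stands nowhere in the protocol. Holding it fixed, and counting only completers, 72 × (1 − d):

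| Loss | Completers | One-tailed power | Difference detectable with 80% power (SD units) |
|---|---|---|---|
| 24% | 54.7 | 0.82 | 0.68 |
| 27.8% | 52.0 | 0.80 | 0.70 |
| 38% | 44.6 | 0.74 | 0.76 |
| 52% | 34.6 | 0.64 | 0.86 |
| 58% | 30.2 | 0.59 | 0.93 |

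**Step 4: the condition itself.** With the stated standardised difference of 0.20, one-tailed 5% and 80% power, about 310 per group are needed, and 26 per group gives power of about 0.18 with no dropout at all. The stated 8.6 points at 0.20 would imply an SD of 8.6/0.20 = 43. So 52 does not follow from the printed inputs either. Steps 1 and 2 do not depend on this; step 3 does.

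**The case against.** Several points can fairly be made for the plan.

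- **The wording sets a minimum, and 72 exceeds the 69 needed at 24%.** True, but the Abstract and Study design fix the trial at 72, so the minimum is the plan.
- **Dropout from therapy is not loss of outcome data.** This stands and limits the size of the effect. The Data analyses section plans intention-to-treat analysis with GEE over three time points, which can use partial data, although the article itself requires missingness to be completely random. Treatment completion is defined by attending at least 8 group sessions, not by returning a BSL-23. The power figures above are therefore nearer a worst case than a forecast of the planned analysis. It does not rescue the inflation step, because the Sample size section itself inflates for dropout in order to keep 52.
- **The risk is disclosed.** The Discussion lists high dropout as a limitation and warns of distorted results. It does not say that 72 fails to cover the quoted range.

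Two stronger readings are tempting, and the documents do not support them. A reader might infer that the trial has 80% power and loses it once dropout passes 27.8%. On the literal inputs that power was never there, since 26 per group at 0.20 gives about 0.18. A reader might also infer that the protocol regards loss above 27.8% as likely. The Discussion does call its range expected, but it gives no distribution over the range and no rate for this trial, and the protocol plans travel support, text reminders and extra sessions to retain participants. The 87% and 89% in step 2 are lengths of an interval, not probabilities.

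**Conclusion.** The point holds as a failure of derivation. Seventy-two does not follow from 52 evaluable and 24% to 52% dropout. It is sufficient only up to 27.8% loss, against requirements of 84 at 38%, 109 at 52% and 124 at 58%. The conflict between 52% and 58% under one citation is an error whatever view is taken of power.

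The effect on power can be stated only conditionally: about 0.74, 0.64 and 0.59 at 38%, 52% and 58% loss. This assumes that 52 evaluable gives 80% one-tailed power (a standardised difference of about 0.70, against the stated 0.20), that dropouts contribute no data, and that losses are equal in the two arms. The effect-size conflict is a separate and prior defect. Until it is settled, these figures show how power falls with attrition, not what the trial's power is.

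**What to change.** Change the Sample size section in this order.

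1. Correct the effect size on which 52 rests, so that later figures have a sound base.
2. State the attrition rate assumed. Define it as loss of BSL-23 data at the primary time point rather than as dropout from therapy. Name that time point, since Sample size refers to 12 months while Study aims places the primary outcome after treatment.
3. Replace the present inference with a conditional statement: 72 randomised yields 52 evaluable only if that loss is no more than 27.8%.
4. Give power and detectable difference at several rates across the quoted range (for example 24%, 38%, 52% and the Discussion's 58%), using the corrected effect size.
5. Check the cited source and make the upper limit the same in Sample size and Discussion.

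The cost of the attrition correction is wording and a short table. It requires no added enrolment. It restores no power; it makes the stated power explicitly conditional on attrition.
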